## Abstract

Sedentary behavior, a key modifiable risk factor for cardiovascular disease, is prevalent among cardiovascular disease patients. However, few interventions target sedentary behavior in this group. This paper describes the protocol of a parallel two-group randomized controlled trial for a novel multi-technology sedentary behavior reduction intervention for cardiovascular disease patients (registered at Clinicaltrial.gov, NCT05534256). The pilot trial (n = 70) will test a 12-week “Sit Less” program, based on Habit Formation theory. The 35 participants in the intervention group will receive an instructional goal-setting session, a Fitbit for movement prompts, a smart water bottle (HidrateSpark) to promote hydration and encourage restroom breaks, and weekly personalized text messages. A control group of 35 will receive the American Heart Association’s “Answers by Heart” fact sheets. This trial will assess the feasibility and acceptability of implementing the “Sit Less” program with cardiovascular disease patients and the program’s primary efficacy in changing sedentary behavior, measured by the activPAL activity tracker. Secondary outcomes include physical activity levels, cardiometabolic biomarkers, and patient-centered outcomes (i.e. sedentary behavior self-efficacy, habit strength, and fear of movement). This study leverages commonly used mobile and wearable technologies to address sedentary behavior in cardiovascular disease patients, a high-risk group. Its findings on the feasibility, acceptability and primary efficacy of the intervention hold promise for broad dissemination.

## Introduction

Cardiovascular disease (CVD) remains the leading cause of death in the U.S. Half of people who survive a heart attack suffer a second heart attack within three years [1], and 15% die from recurrent heart attacks [2]. Moderate-to-vigorous levels of physical activity (PA) can significantly reduce reinfarction and cardiac mortality [3], and therefore, moderate-to-vigorous levels of PA >150 minutes per week is recommended for CVD patients [4, 5]. However, only 10–21% of CVD patients meet the PA recommendations [6, 7] and they still spend 10–11 hours on sedentary behavior [6, 8–10]. Common barriers to physical activity include fear of reinfarction, shortness of breath, fatigue [11, 12], and time and cost related to exercise [12, 13]. Thus, there is an urgent need to find innovative ways of engaging this population in achieving more active lifestyles.

In people with CVD, sedentary behavior takes up to 70–90% of waking activities [6, 8–10] and 50% of sedentary behavior is prolonged (>30 minutes per bout) [8]. During sedentary time, there is no muscle contraction of the legs, which causes decreasing insulin sensitivity, vascular dysfunction, and activation of low-grade inflammatory cascades [14]. As a result, greater total sedentary time is related to increased CVD risk [15], including decreased high-density lipoprotein (HDL) and increased triglycerides (TG), fasting glucose [16], BMI, and waist circumference (WC) [17]. Prolonged sedentary time is also associated with a 12% higher risk of incidental CVD [18] and an increased risk of CVD mortality regardless of PA levels [19, 20].

Reducing sedentary time with frequent bouts of standing or walking is safe and feasible for patients with chronic diseases [8, 21, 22]. Emerging evidence from meta-analyses and intervention studies conducted in free-living environments indicate significant beneficial relationships of sedentary breaks with BMI, waist circumference, and C-reactive protein (CRP) [23], as well as average glucose levels, insulin and blood pressure (BP) [23–25]. Therefore, frequent sedentary breaks can not only reduce the total sedentary time and increase total standing and walking time, but also break prolonged sitting time, bringing additional cardiometabolic benefits and possibly overcoming common barriers to moderate-to-vigorous PA.

Frequent sedentary breaks can be achieved through an innovative wearable and mHealth approach. For example, utilizing wearables allows people to self-monitor their sedentary time and provides walking prompts to break sedentary behavior. In addition, by utilizing smart water bottle technology, individuals can increase their water intake, which leads them to walk to the restroom more frequently. This can be a natural motivator to break prolonged sitting bouts. A weekly tailored text message based on wearables’ data can motivate participants in reducing sedentary behavior. This multifaceted strategy offers a low-cost, sustainable method for sedentary behavior reduction for CVD patients, who are typically over 60 years old, yet lacks widespread implementation in this age group. While some research has focused on reducing sedentary behavior in CVD patients [8, 9, 26, 27], it predominantly involves individuals already participating in cardiac rehabilitation. Given that these participants tend to be motivated and exhibit higher physical activity and lower sedentary time during rehabilitation, there is a lack of information on how to extend these findings to the broader CVD patient population who may not be as inclined to enroll in cardiac rehabilitation programs.

To respond to these gaps in patient resources and the literature, we developed a multi-technology-based, individually tailored sedentary behavior reduction intervention for people with CVD. The intervention incorporates a coaching session, a wearable fitness tracker (Fitbit Inspire 2), a smart water bottle (HidrateSpark), and individually tailored text messages. The aim of the current paper is to detail the study protocol for the pilot randomized controlled trial (RCT) testing the feasibility, acceptability, and preliminary efficacy of this intervention.

## Materials and methods

### 2.1. Study design

The research study is a single-center, parallel two-group RCT (registered at Clinicaltrial.gov on September 6, 2022, NCT05534256). The research study will adhere to the CONSORT (Consolidated Standards of Reporting Trials) Statement. The study protocol follows the SPIRIT (Standard Protocol Items: Recommendations for Interventional Trials) 2013 Statement (S1 Checklist). The schedule of enrollment, interventions, and assessments is described in Fig 1. This study was reviewed and approved by the Vanderbilt University Medical Center IRB (#220416). Participant recruitment began on September 13, 2022, and is anticipated to end by March 31, 2025.

**Fig 1 pone.0302582.g001:**
[figure not shown]
Time schedule of enrollment, interventions, and assessments followed by the SPIRIT 2013 reporting guideline. *CGM = Continuous Glucose Monitoring.

### 2.2. Participants and sample size

We will recruit 70 patients with CVD who 1) are 18 years or older, 2) have at least one of the following conditions: history of heart attack, coronary/carotid artery disease, ischemic heart disease, peripheral artery disease, a stent placed in the heart or leg or had a coronary artery bypass surgery, 3) self-report of sitting ≥ 8 hours/day, 4) ability to stand and walk, and 5) ownership of a smartphone. We will exclude those who are 1) using an activity tracker, 2) currently participating in exercise or cardiac rehabilitation programs, 3) non-English speaking, 4) classified as unstable (e.g. heart failure, uncontrolled arrhythmia), have kidney disease that limits daily water intake, or any conditions that prevent standing or walking due to physical or cognitive limitations, such as cognitive impairment, severe pain, problems with lower limbs, or a history of surgeries that limit movement, and 5) currently pregnant.

As a pilot/feasibility study, we do not propose a fully powered, hypothesis-testing trial. The primary outcome of this study is the feasibility and acceptability of the Sit Less program, which is not dependent on effect sizes. Therefore, we did not calculate the sample size based on the effect sizes but based on the calculation to identify potential problems in feasibility/acceptability. According to Viechtbauer et al. [28], if the feasibility issue occurs with a 10% chance, a sample size of 30 is required to identify the feasibility issue with a confidence of 95%. The total sample of 70 (35 in the intervention group and 35 in the control group) was estimated to allow sufficient piloting of study protocols and examination of the feasibility of intervention activities and measures to inform future research.

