### 2.4. Baseline visits

All interested respondents will be screened by a trained research staff member over the phone to confirm their eligibility, which includes the ability to walk and stand without limitations. Eligible participants will be invited to the initial in-person baseline visit at the Vanderbilt University School of Nursing (VUSN) Research Clinic (Nashville, TN). The study flow is illustrated in Fig 2.

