#### 2.6.1. Theoretical framework

The Sit Less program employs a Habit Formation framework [31] to target the habit-like nature of sedentary behavior, which often occurs without conscious thought or intention [32, 33]. The program focuses on making individuals aware of their sedentary habits and encourages the adoption of new behaviors, such as taking breaks to stand or walk, through consistent practice in specific contexts. According to the Habit Formation framework [31], habit formation involves four phases: motivation, action initiation, behavior repetition in a context, and cue-association building. Through this process, over time individuals may rely on contextual cues rather than conscious self-regulation to initiate a behavior, making it potentially easier to perform and more sustainable with consistent environments [31]. The Habit Formation framework is widely used for sedentary behavior reduction in older adults [32].

The framework guides our intervention by: 1) bringing sedentary behavior into conscious awareness through prompts (e.g., vibrations from a Fitbit), and 2) making a new habit of sedentary breaks (5 minutes of standing/walking every 30 minutes of sitting) through context-dependent repetition (e.g., during TV commercials). To enhance habit formation, behavioral techniques supporting motivation and action planning will be used (Table 1) [34].

**Table 1 pone.0302582.t001:** Relationship between intervention components, theoretical constructs, and behavioral techniques.

Intervention component	Theoretical constructs	Behavioral change techniques
**Instructional/ goal setting session**	Motivation, define context and target habitual behavior	Goal setting, instruction on how to perform behavior, information on health consequences, identification of targetable prolonged sitting
**Activity tracker**	Awareness of unconscious sitting habits, gradually develop a new habit of sedentary breaks through repetition, develop a contextual cue-behavior association	Use of sedentary break prompts and cues, context-dependent repetition, self-monitoring, feedback on behavior
**Smart water bottle**	Motivation (I have to get up to go to the restroom), gradually develop a new habit of drinking water	Use of cues through change of bottle color (time to drink water)
**Weekly tailored text message**	Motivation, translate intention into action, enhance contextual cue-behavior association	Feedback on behavior, problem solving, review of goal, setting of new goal

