#### 2.6.4. Smart water bottle

We will provide a smart water bottle (HidrateSpark, U.S.A) to each participant in the intervention group as a natural motivator to have sedentary breaks. The device alerts participants with a color change and message on the Fitbit to keep them hydrated. The device provides the daily water intake summary in the Fitbit app. The app calculates an individualized water intake goal based on the participant’s weight, age, and activity levels. By increasing water intake, participants will need to get up more frequently to use the bathroom and to refill their water bottles, which will break their prolonged sedentary behavior.

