#### 2.14.2. Harms and auditing

The study team, along with the PI, will hold weekly meetings to assess the progress of the study, and review any potential problems or adverse events. Expected adverse events include muscle soreness, discomfort from frequent sedentary breaks, skin irritation from the activPAL and Fitbit, and local redness, inflammation, or bleeding at the CGM sensor site. Serious and unexpected adverse events related to the study protocol will be reported to the IRB within seven days. Annually, the study will undergo continuing review and be granted approval by the IRB.

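### Minor patient-safety point: the water-intake exclusion names kidney disease as the only cause, although the intervention deliberately increases drinking

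*Protocol article*

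**What the plan says.** Section 2.2 of the protocol article lists five exclusion items. Only item 4 mentions water. It excludes those "classified as unstable (e.g. heart failure, uncontrolled arrhythmia), have kidney disease that limits daily water intake", and then goes on to conditions that prevent standing or walking. The other four items concern activity-tracker use, exercise or cardiac rehabilitation programs, language and pregnancy.

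Section 2.6.4 supplies the bottle "to each participant in the intervention group as a natural motivator to have sedentary breaks". It adds: "The device alerts participants with a color change and message on the Fitbit to keep them hydrated". On the target it says: "The app calculates an individualized water intake goal based on" weight, age and activity levels. The same section gives the mechanism: more water means more trips to the bathroom and to refill. Table 1 in section 2.6.1 lists, among what the bottle is meant to achieve, "gradually develop a new habit of drinking water".

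Under section 2.4, interested respondents are "screened by a trained research staff member over the phone to confirm their eligibility". The ability named there is walking and standing. Under section 2.14.2 the team meets weekly to "review any potential problems or adverse events".

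**The concern.** The kidney clause evidently exists to keep people who must limit their water intake away from a component designed to make them drink more. What makes the bottle unsuitable for such a person is the limit, whatever its cause. The clause is written around one cause.

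A patient told to limit fluids for a reason that item 4 does not reach meets no stated exclusion. If randomized to Sit Less, that patient receives prompts to drink and a numerical goal that, as described, takes no account of the advice. Because research staff confirm eligibility by phone, the wording they apply matters.

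What is at stake is patient safety on a small scale, not the validity of any result.

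**Working it through.** No figure in the article is at issue, so the check is a reading of each criterion against the exposure.

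1. **Is the exposure intended?** Yes. Section 2.6.4 presents higher water intake as the means of breaking up sitting, and Table 1 lists a drinking habit as a target. The bottle goes to everyone in the intervention arm.

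2. **Does the goal allow for a medical limit?** The inputs listed in section 2.6.4 are weight, age and activity levels. A fluid limit is not among them, and the article describes no cap on the goal and no check with a care provider.

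3. **Which exclusions could reach a patient with a fluid limit?**
   - Items 1, 2, 3 and 5 (tracker use, exercise or rehabilitation, language, pregnancy) do not concern fluid.
   - Item 4, kidney clause: reaches the limit only if kidney disease causes it.
   - Item 4, instability clause: names heart failure and uncontrolled arrhythmia as examples. The plainest reading excludes all heart failure. Because heart failure is given as an example of being unstable, a screener could instead read it as excluding only unstable heart failure.
   - Item 4, remainder: covers conditions that prevent standing or walking, and says nothing on fluid.

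4. **Who is left?** On the plain reading, someone whose fluid limit comes from neither kidney disease nor a condition classed as unstable. On the narrower reading, also someone with stable heart failure and a fluid limit.

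5. **Do other stated safeguards close the gap?** The instruction in section 2.6.2 to stop if unwell concerns the standing and walking activities. The expected adverse events in section 2.14.2 (muscle soreness, discomfort from breaks, skin irritation, sensor-site reactions) include nothing related to fluid. Weekly adverse-event review does apply, but it acts after exposure.

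6. **Does the sample-size statement depend on this?** No. It rests on a 10% problem rate and 95% confidence: n = ln(1 − 0.95) / ln(1 − 0.10) = 28.43, rounded up to 29, against 30 stated. Neither input involves the eligibility wording.

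**The case against.** The strongest reply is that this is a condensed article. It contains no false statement and no contradiction here, and a rarer fluid limit could be handled by screening questions, clinician discretion or bottle instructions in the full protocol. That stands, and nothing is claimed about those documents. But the article does state this exclusion, and it states it by cause. Choosing too narrow a rule is different from leaving out a detail.

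Second, the uncovered group may be empty. The two causes the text itself points to are dealt with, and the instability clause is open-ended, so it may catch other conditions. This also stands, and it is why the point is minor. The article gives no share of patients with such a limit, so any probability of enrolling one would only restate an assumption.

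Third, no harm is documented. Participants are prompted, not required, to drink. Section 2.9.1 counts Fitbit wear and replies to goal-setting texts as compliance, not water intake. Medical history and medication are collected (section 2.11), though the article does not say that they feed into eligibility. All of this is fair.

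A reader might infer that heart-failure patients on fluid restriction are being admitted. The text does not support that: heart failure is named in the same item and is most plainly excluded. A reader might also infer that the phone call is the only safeguard. The article does not say so.

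**Conclusion.** The point holds as a cheap improvement to patient safety. The stated exclusion covers a limit on water intake only when kidney disease causes it, while the intervention sets out to increase drinking.

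Its size is small and possibly zero, and the article gives no number from which to estimate it. The conclusion rests on two readings: that the kidney clause is there because of the bottle, and that the app goal uses only the inputs section 2.6.4 lists.

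It would go too far to say that fluid-restricted patients will be enrolled or harmed, or that any trial result is affected. The documents show only that such a patient, if one presented, might meet no written exclusion. Outcomes, analyses, compliance measures and the sample size are untouched.

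**What to change.** In exclusion item 4, replace the kidney-disease clause with: *any condition or medical advice that limits daily water intake (e.g. kidney disease)*. This ties the rule to the limit itself. It also covers stable heart failure with a fluid limit, however the instability clause is read.

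Apply it to participants not yet enrolled and carry it into the future trial. The article states: "Participant recruitment began on September 13, 2022, and is anticipated to end by March 31, 2025". The change cannot protect anyone already enrolled, and if recruitment has closed its value lies in the next protocol.

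The cost is one amendment with IRB approval, which section 2.15.1 requires for any protocol change, and possibly a few extra screens to replace people newly excluded. No analysis needs to be rewritten.

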### 2.3. Recruitment

#### 2.3.1. Off-line recruitment

Recruitment flyers and brochures will be posted in cardiology outpatient clinics at Vanderbilt Heart (Nashville, TN, U.S.A) for self-referrals. In addition, the patient care providers will also reach out to their patients and provide their patients with our study brochure to allow the patient to contact the study team. We will also prescreen potential participants using the Epic medical records system for potential patients’ contact information. Initially, the study team will send an opt-out letter to the potential patients. If the patients do not contact the study team within two weeks by email or telephone call to opt-out, the trained research staff will call them, explain the study, and screen for interest and eligibility.

#### 2.3.2. On-line recruitment

We will send a message to potential participants who are registered in the Vanderbilt community-wide email distribution list and ResearchMatch (national web-based recruitment tool). Due to the in-person nature of the protocol, we will only contact those who are living in Nashville or surrounding areas. In the invitation email, there will be a link directing potential participants to the prescreening survey via REDCap. This pre-screening data will be saved into REDCap. Once they meet all the inclusion criteria, the trained research staff will call them to confirm their eligibility.

### 2.4. Baseline visits

All interested respondents will be screened by a trained research staff member over the phone to confirm their eligibility, which includes the ability to walk and stand without limitations. Eligible participants will be invited to the initial in-person baseline visit at the Vanderbilt University School of Nursing (VUSN) Research Clinic (Nashville, TN). The study flow is illustrated in Fig 2.

**Fig 2 pone.0302582.g002:**
[figure not shown]
Study flow. B1 = Baseline visit 1, B2 = Baseline visit 2, F1 = Follow-up visit 1, *CGM = continuous glucose monitor.

#### 2.4.1. Baseline visit 1

At Baseline Visit 1, eligible individuals will complete the written informed consent with assistance from the trained research staff. Those who are consented and complete the baseline survey questionnaires will commence a 7-day usual physical activity and glucose monitoring period. During this period, all participants will wear an activPAL3 device (PAL Technologies) on the thigh and a continuous glucose monitor (CGM, Abbott FreeStyle Libre Pro) on the upper arm and follow their usual diet and activity. Participants will receive $25 for the completion of the Baseline Visit 1.

#### 2.4.2. Baseline visit 2

After 7 days of activity and glucose monitoring, the participants will return to the VUSN Research Clinic. Baseline anthropometric assessments, blood pressure, and blood collection via finger prick will be completed. The activPAL and CGM will be removed at this visit. Participants will receive $25 for Baseline Visit 2.

### 2.5. Randomization

By using the REDCap randomization module, computer-generated random numbers will be created by a statistician. During Baseline Visit 2, randomization to the intervention and control arms (1:1) will be performed by a study team member. A study team member will click REDCap’s randomization function and each participant’s group assignment will be available online via REDCap. The study team member will immediately inform participants of their group assignment during Baseline Visit 2. Participants and interventionist will not be blinded to the allocation due to the nature of the intervention program. However, outcome assessors and data analysists will be blinded to the allocation.

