#### 2.6.3. Activity tracker

A Fitbit Inspire 2 (Fitbit Inc., U.S.A) will be provided to each intervention participant. This device alerts participants with a vibration and message on the watch face when they have been sitting for 60 minutes (i.e., “Move alert”). Participants can select the days and the time ranges to receive the move alerts. Fitbit provides sedentary behavior statistics including the longest sitting period (“Longest Stationary Period”) and total daily sitting hours (“Stationary Hours”) in the app. Participants will be encouraged to check the Fitbit app at the end of the day to monitor their longest sitting period and total daily sitting hours. They will be guided to apply the TTT booklet tips to interrupt their longest sitting period and decrease total daily sitting hours, aiming to achieve their overall goals of a total of 120 minutes of sedentary behavior reduction and having 5 minutes of a sedentary break every 30 minutes by the end of the intervention.

To ensure consistent use of the Fitbit, participants will be instructed to wear the device during waking hours, including while showering or swimming. They will also be encouraged to wear the Fitbit at night, although this is optional. Participants are required to charge the Fitbit once a week, and we will send a text message every Sunday reminding them to charge and sync their Fitbit. We will track participants’ wear status over 12 weeks. If a participant fails to sync their Fitbit or wear it for two consecutive days, they will receive an automated reminder text message. If no improvement is observed within another two days, research staff will contact the participant by phone to troubleshoot issues.

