### 2.8. Post-intervention visit

After 12 weeks of the intervention, all participants will be invited to an in-person visit at week 13. During the visit, all the above parameters will be re-measured by the same RA and all the above survey questionnaires will be completed. All participants will then wear the activPAL3 and the CGM for another 7 days to examine their post-intervention activity and glycemic control. They will return the devices via pre-paid mail. To enhance adherence to the protocol, all participants will receive $50 for the post-intervention visit, and an additional $50 for mailing the devices back to the study team (a total compensation = $150 per participant). A subsample of participants from the intervention group (n = 20) will be invited to participate in an exit interview.

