### 2.12. Data management plan

Study participants will complete questionnaires online via REDCap, and the study team will review the responses in the presence of the participants to clarify or complete any missing information. REDCap, a secure, HIPAA-compliant web-based application developed at Vanderbilt University, will be used to manage all data. It provides data entry, audit trails, and export procedures, and flags inconsistent or out-of-range responses for review.

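### Section 2.5 claims blinded outcome assessors, but the week-13 procedures make this hard to maintain for tape measurements and staff-reviewed questionnaires

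*Protocol article*

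**What the plan says.** All references are to the protocol article.

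- **Blinding claim (2.5).** "Participants and interventionist will not be blinded to the allocation due to the nature of the intervention program". The next sentence adds, without limiting it to particular outcomes: "However, outcome assessors and data analysists will be blinded to the allocation".
- **Allocation (2.5).** "During Baseline Visit 2, randomization to the intervention and control arms (1:1) will be performed by a study team member". Disclosure is at once: "The study team member will immediately inform participants of their group assignment during Baseline Visit 2". After that, "each participant’s group assignment will be available online via REDCap".
- **Baseline physical measures (2.4.2) and coaching (2.6.2).** Both take place at that same Baseline Visit 2. The PI gives the coaching session.
- **Week-13 visit (2.8).** "all the above parameters will be re-measured by the same RA and all the above survey questionnaires will be completed".
- **Questionnaires (2.12).** Participants complete them online in REDCap, and then "the study team will review the responses in the presence of the participants to clarify or complete any missing information".
- **Fitbit (2.6.3).** In the intervention arm, "participants will be instructed to wear the device during waking hours". Section 2.2 excludes people who already use a tracker.
- **Satisfaction items (2.9.1).** They ask about the Fitbit, its app and move alert, the water bottle and the text messages. At least 75% of participants must agree, or agree strongly, with each statement.

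**The concern.** The blinding sentence is a positive claim about bias control that a results paper will probably repeat. If the person holding the tape or going over the answers can tell the arm, small unintended differences in measurement or prompting can favour the program while the report calls those outcomes blindly assessed.

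Two uses of the data are at stake. Section 2.13 compares the arms on the key study outcomes at p < 0.05 without multiplicity adjustment and carries the adjusted mean differences forward to inform later trials. Section 2.9.1 judges acceptability, a primary outcome, on satisfaction answers that staff may discuss with the participant.

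**Working it through.** The plan gives no figure for this point, so the main check sets the sections side by side.

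**Routes by which an assessor could learn the arm**

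1. *Same person, same visit.* Baseline physical measures, randomization, disclosure and coaching share Baseline Visit 2 (2.4.2, 2.5, 2.6.2), and the same RA returns at week 13 (2.8). This creates an opportunity to learn the arm. It does not show that the RA did.
2. *Visible device.* Because tracker users are excluded (2.2), a wrist Fitbit at week 13 points to the intervention arm. The wear instruction and wear tracking belong to the 12 intervention weeks. However, 2.8 has participants post back only the activPAL and glucose monitor, and 2.9.1 asks whether they would go on wearing the Fitbit. Some may well arrive wearing it.
3. *Face-to-face review.* Anyone who goes over satisfaction items naming the Fitbit, bottle and texts learns the arm. Section 2.12 assigns review to the study team without saying who, or whether it follows the physical measures.
4. *Shared roles.* Research staff telephone participants about Fitbit non-wear (2.6.3), may run the intervention-only exit interviews (2.9.1) and collect the blood samples (2.10.2).

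**Exposure by outcome (2.9 and 2.10)**

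| Outcome | How obtained | Exposure |
|---|---|---|
| Waist and hip circumference | Tape, read by the assessor | Main physical exposure |
| Self-efficacy, habit strength, fear of movement, PHQ-9 | Self-report by unblinded participants, then staff review | Open to prompting; self-report itself is unblinded whoever assesses |
| Satisfaction items | Self-report; staff review if 2.12 covers them | Open to prompting; feed the 75% threshold |
| Blood pressure | Mean of three automated readings | Small |
| activPAL, glucose monitor, laboratory assays | Device or external laboratory | Not material |

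**Illustrative size for a between-arm outcome**

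Inputs: 35 per arm (2.2), two-sided 5% level (2.13). The shift d, in SD units, is an assumption.

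- SE = sqrt(1/35 + 1/35) = sqrt(2/35) = 0.239 SD.
- Rejection rate with no true effect = P(Z > 1.96 − d/0.239) + P(Z < −1.96 − d/0.239).
- d = 0.1: d/SE = 0.42, rate about 7%.
- d = 0.2: d/SE = 0.84, rate about 13%.
- d = 0.3: d/SE = 1.26, rate about 24%.

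This is not the planned test. Section 2.13 adjusts for baseline and omits participants without a post-intervention value, whereas the calculation is unadjusted and uses all 35 per arm.

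**Illustrative size for acceptability**

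If all 35 intervention participants answer, 0.75 × 35 = 26.25, so 27 must agree with a given statement. 26/35 = 74.3% misses the threshold and 27/35 = 77.1% meets it. Near the boundary, one prompted answer decides a statement.

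**The case against.** The strongest reply is that nothing in the article directly contradicts the blinding sentence. A reader might infer that the week-13 visit, as described, shows the assessor the allocation. The text does not support that. An unnamed study team member randomizes and discloses, and the PI coaches. The RA is nowhere said to do either, to see the REDCap assignment, or to review the satisfaction items. The reference in 2.8 to questionnaires already mentioned may not include the satisfaction items, which first appear in 2.9.1. The Fitbit instruction is tied to the 12 intervention weeks. All of this stands, so unblinding is a likely consequence and not a stated one.

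A reader might also infer that blood pressure and all self-reported outcomes lose a protection they were promised. That goes too far. Blood pressure comes from an automated monitor, and 2.5 openly says participants are unblinded, so assessor blinding was never going to protect self-report. What remains for the questionnaires is the added risk from staff review.

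It can further be said that role separation, access rights and visit order are details for the full protocol. As mere omissions they would be no finding. But the article itself makes an unqualified claim and itself describes a returning RA and face-to-face review that work against it.

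Finally, keeping the same RA has real value for measurement consistency, and staffing is not described. Asking for a different assessor is therefore not warranted.

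**Conclusion.** The point holds in limited form. The unqualified assessor-blinding claim is hard to maintain at week 13 under the described procedures. The consequence falls mainly on tape-measured waist and hip circumference and on questionnaires open to staff prompting, including any satisfaction items reviewed in person.

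The activPAL sedentary outcomes are not materially affected. Acceptability is the one primary outcome touched, and only if the in-person review extends to the satisfaction items.

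The article gives no basis for the size of any bias. The rates of 7%, 13% and 24% show what assumed shifts of 0.1 to 0.3 SD would do in a simple unadjusted comparison at full sample size. They should not be read as estimates for this trial or applied equally to every outcome.

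**What to change.** 1. **Visit order.** At week 13, take the physical measures first, with the Fitbit and bottle out of sight, before any questionnaire is opened. Keep the same RA, provided that RA has no part in randomization, coaching or Fitbit telephone calls.
2. **Questionnaire review.** Replace the in-person staff review in 2.12, above all for the satisfaction items, with required-field checks in REDCap, where participants already complete the forms.
3. **Blinding sentence.** Limit 2.5 to device processing, laboratory assays, data analysis and physical measures taken under step 1. State that participant-reported outcomes are not blinded.

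The cost is a visit-order instruction, a REDCap setting and a corrected sentence. The downside is slightly more unclarified or missing questionnaire data, which matters somewhat because 2.13 allows no imputation; required fields should recover part of it.
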